### Recruitment

The training will be advertised by hospital administrators, class representatives, and regional traffic law enforcement leaders, and course participants will be recruited by the principal investigator and the respective hospital administrators. The patient participants will be recruited by dedicated project officers at the accident and emergency departments.

### Assignment of Interventions: Allocation

#### Sequence Generation

We will perform cluster randomization for a permuted block size of 6 hospitals (clusters) using an open-source simulation software [41], with seed numbers that will be kept confidential to the offsite study administrator. A list of 6 random codes will be generated to assign hospitals to the intervention or control group. As we plan to perform analyses at both the individual level and treatment arm level, we will not add any stratification factors in the simulation model.

#### Concealment Mechanism

The allocation sequence and assignment codes will be generated by and kept secret by an offsite study administrator. Both outcome assessors and patient participants will be blinded to the treatment allocation.

#### Implementation

Trainee participants will be enrolled by the respective university hospital administrators, whereas patient participants will be enrolled by project medical officers at the respective study sites, who will serve as outcome assessors.

### Assignment of the Intervention: Blinding

#### Who Will Be Blinded

Trial patient participants and outcome assessors will be blinded using blocked allocation sequence codes.

#### Procedure for Unblinding if Needed

Unblinding will only be permissible in the likely occurrence of adverse events among the study participants, which can be directly attributed to the study intervention. Such events will be discussed with the attending physicians. Otherwise, the allocation codes will only be revealed to the biostatistician at the time of interim analysis when half of the sample size is recruited. At this point, unblinding the biostatistician is considered more beneficial to inform termination or continuation of the trial, which outweighs the perceived fear of unknown bias [42].

### Data Collection and Management

#### Plans for Assessment and Collection of Outcomes

Data collection will start simultaneously at all the study sites. Medical officers (blinded outcome assessors) with a minimum qualification of Bachelor of Medicine and Bachelor of Surgery (MBChB) and at least 2 years of clinical experience will prospectively collect data through clinical observations, interviews, home visits, and extraction from hospital and police records. All outcome assessors must be willing to undertake a 1-day budgeted training in the use of data collection tools for this trial and the World Health Organization (WHO) ICD-10 online coding module. The data will be collected daily as medical trainees and interns will attend clinical rotations every day. Upon obtaining informed consent, the venue for data collection, including follow-up information, will be at accident and emergence departments during admission, surgical wards, and outpatient clinics, as well as through home visits and phone calls to patients, care takers, or recipient hospital physicians in the case of referrals.

The study variables will include sociodemographic and clinical variables, such as sex, age, injury mechanisms, including nature of collision and road user category, time of injury, prehospital transit time, prehospital care, mode of arrival, vital signs, nature of physical injuries, radiological findings, and injury severity based on the GCS score and Kampala Trauma Score (KTS) [43]. In addition, data on the nature of the treatment administered; need for referral; referral-exit interval; and outcomes, including the TOMS, GOS score, mortality, and time from injury to death, will be obtained. The data collection tools that will be used in this trial, such as the GCS, GOS, TEFS, TOMS, and KTS, have been shown to demonstrate excellent criterion internal validity, consistence, and reproducibility in previous studies [28,29,43,44].

Further, the tools are recognized for their high interrater reliability, sensitivity to change, and ability to be used as continuous or categorical variables in validation studies [28,29,43,44]. The baseline TEFS, GCS score, and KTS will be added as covariates whose interaction and confounding will be assessed and controlled since the inclusion of baseline values of outcomes as covariates is arguably one of the strongest factors to reduce ICC estimates [45]. The difference in distribution of baseline characteristics will be compared using means (SDs), medians (IQRs), and ranges for quantitative data; otherwise, frequencies and percentages will be used for categorical variables. All data collection forms for this trial and detailed definitions of assessment tools for patient and trainee participants are available in Multimedia Appendix 5 and Multimedia Appendix 6, respectively.

#### Plans to Promote Participant Retention and Complete Follow-Up

Coffee breaks will be facilitated during training to optimize participation. Phone and email contacts will be obtained from all medical trainees and law enforcement professionals. In addition, 2 phone contacts will be obtained for each patient participant at the time of enrollment at accident and emergency departments (ie, the patient and their next of kin or legally authorized representative who will in turn be provided with the phone contact of the study nurse coordinators for the purpose of follow-up). Automated reminders will be sent to data collection assistants through mobile phones and the research electronic data capture (REDCap) platform.

Where applicable, home visits will be conducted for participants who are unable to turn up for appointments because of their disability. Transport costs will be reimbursed for traffic law enforcement professionals and patient participants turning up for appointments outside of the routine hospital visits. Participants will be considered as lost to follow-up if they are untraceable by phone, clinic appointment, or home visit. Data on the baseline sociodemographic and clinical characteristics of those lost to follow-up or those who discontinue because of a breach of the intervention protocol will be retained for comparisons between groups, but the data of those who withdraw their consent will be deleted.

### Patient and Public Involvement

Using semistructured questionnaires and semistructured interviews, a 1-day consultative meeting will be conducted at each study site with chief residents, heads of interns, patient caregivers, student representatives, and regional traffic police commanders in the month preceding study commencement to discuss their perceived barriers to injury care in order to uncover themes for potential sources of delays ranging from accident scene discovery, evacuation, and prehospital transportation to emergency care, which shaped the final data collection tools.

During this engagement, trainee and caregiver representatives will provide insights on the feasibility of the outcome assessment tools and the time commitment required to respond to the questionnaire, which will inform the data collection time points of day 1, the first week, and day 90. This strategy will strike a balance regarding the feasibility of maximizing response rates and obtaining data while not overloading the already scarce human resources of traffic law enforcement, and trainees and clinicians at accident and emergency departments. Further engagements will be made during RTTDC training sessions and audit meetings, during which bidirectional feedback will be provided on team performance, challenges with individual team dynamics, and proposed areas of improvement to help shape future training. The results of patient and public engagement will be reported in an ancillary study on the barriers to injury care.

### Data Management

Due to expected network breakdowns in rural centers, data will be collected in hard copies, coded, and entered into the REDCap secure virtual network hosted by the University of Turku. Data entry will be performed by outcome assessors who will be issued with a confidential login password for REDCap. Later, the data will be exported to Stata version 15.0 (StataCorp) for analysis. The REDCap software was preferred owing to its presumed secure web-based intuitive interface for validated data capture, offering an additional advantage to prohibit dual entry, restrict values, calibrate data ranges, and retrieve audit trails for tracking data manipulation [46]. Further, the software permits seamless data export and download procedures that are compatible with Stata, while allowing for data integration and interoperability with external sources [47]. Any data errors will be resolved during weekly audit meetings in reference to the online codebook with a visible description of variables accessible to the principal investigator and all outcome assessors.

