To enable an active “alarm” activation criterion for the trauma committees, closed-loop communication, and a smooth “handover” process from police officers to medical trainees prior to patient transfer, the trained traffic officers on highways will serve as focal contact persons for the rural trauma teams from the parish (subcounty) level. In the event of a road traffic accident, teammates will freely contact each other both within and across teams to coordinate evacuation, consultation, referral, and arrival at recipient centers, with the support of trained interns and surgery residents as team leaders. Weekly audit meetings will be conducted remotely via Zoom (Zoom Video Communications) to discuss team challenges, otherwise a trained surgery resident will be available 24/7 to advise on referrals, transfers, and treatments in liaison with consultants who may be physically or remotely available. The control hospitals in this trial will be allowed to provide routine standard care without the RTTDC intervention as summarized in Figure 1.

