### Oversight and Monitoring

#### Composition of the Coordinating Center and Trial Steering Committee

The principal investigator and a central study administrator will form a steering committee that will run the day-to-day activities of the trial. The trial will have 2 onsite overseers and 2 off-site supervisors. In addition, the principal investigator will provide organizational support to rural trauma teams at the intervention study centers through weekly audit meetings. Each of the rural trauma teams is composed of a road traffic law enforcement professional, a third-year medical student, a fifth-year medical student, an intern doctor or nurse, and a specialty surgery resident.

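### Data errors are resolved in meetings otherwise described only as intervention-arm team support, and allocation codes cannot blind assessors who work in the study hospitals

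*Protocol article*

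**What the plan says.** On data cleaning, the Data Management section states: "Any data errors will be resolved during weekly audit meetings in reference to the online codebook". The codebook is "accessible to the principal investigator and all outcome assessors". The same section says: "Data entry will be performed by outcome assessors who will be issued with a confidential login password for REDCap".

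On the meetings, the Intervention Description states: "Weekly audit meetings will be conducted remotely via Zoom (Zoom Video Communications) to discuss team challenges". The section on the coordinating center and steering committee says that "the principal investigator will provide organizational support to rural trauma teams at the intervention study centers through weekly audit meetings". The Patient and Public Involvement section pairs the course sessions with "audit meetings, during which bidirectional feedback will be provided on team performance". No weekly audit meeting is described for the control hospitals, which give routine care without the intervention.

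On blinding, the section Who Will Be Blinded states: "Trial patient participants and outcome assessors will be blinded using blocked allocation sequence codes". The Concealment Mechanism section and the section on outcome collection also call the assessors blinded. The Implementation section says that "patient participants will be enrolled by project medical officers at the respective study sites, who will serve as outcome assessors".

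**The concern.** One term covers two activities: cleaning the trial data, and supporting and giving feedback to the teams whose performance the trial measures. If they share a meeting, the people who record outcomes may learn the arm there, or records may be queried by one route in one arm and by another, or none, in the other.

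Both primary outcomes are intervals between clock times, taken from observation, interviews and hospital and police records. The section on adherence also treats the speed with which a referral is carried out as a measure of how well trained providers apply the course. A forum that discusses team performance is therefore a poor place to correct those times.

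The blinding claim matters in its own right. The TOMS at day 90 is reported by patients to the assessors, and some of the time data come from interviews. An assessor who knows the arm can influence both without intending to.

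**Working it through.** No figure in the protocol depends on this point, so there is nothing to recompute. The check sets the statements side by side.

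**Part 1: the meetings**

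1. Data Management sends all data errors to weekly audit meetings and describes no other route.
2. The two other places that mention weekly audit meetings are the Intervention Description and the steering committee section. The first lists them as a component of the intervention. The second ties them to the intervention centers. Patient and Public Involvement mentions audit meetings without the word weekly, so it supports the link only weakly.
3. No sentence separates a data meeting from a team meeting, and none says who attends when errors are resolved.
4. Taking them as one forum leaves two cases:
   - *Assessors from all six hospitals attend.* Data handling can then be equal, but the assessors meet the trained teams and can tell which hospitals are in the intervention arm. This contradicts the blinding statements.
   - *Only intervention-site assessors attend.* Control-site assessors learn nothing there, but control data have no stated route for resolving errors, so cleaning may differ by arm.
5. The two harms are largely alternatives. Neither case is free of both.
6. If two separate meetings share a name, neither harm follows, but the text does not say so.

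**Part 2: the blinding claim**

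This part needs no assumption about the meetings.

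1. Assessors are project medical officers at the study sites (Implementation) and collect data daily (section on outcome collection).
2. At intervention hospitals, the 2-day course is given on site, aiming for at least 80% of each cohort of eligible surgical trainees, with cohorts identified every 1 to 5 months (Intervention Description). The Sample Size section plans on 3-monthly training cohorts over 36 months: 36 / 3 = 12 periods.
3. Trained teams then work in those hospitals with police contacts, and a trained resident is on call around the clock (Intervention Description).
4. A code conceals the label of an arm in a list or data set. It cannot conceal a recurring course and a visible team structure from a doctor working daily in the same hospital.

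**Which outcomes are exposed**

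| Outcome | How obtained | Exposure to an unblinded assessor |
|---|---|---|
| Primary time intervals | Observation, interview, hospital and police records | Mainly the interview-based part |
| TOMS at 90 days | Reported by the patient to the assessor | Yes |
| Glasgow Outcome Scale at 90 days | Documented by attending clinicians | Not mainly through the assessor |
| Mortality at 90 days | Objective event | Little |

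**The case against.** A reader might infer that the blind fails in these meetings and that cleaning does differ between arms. The text does not support this. It never says that trauma teams are present when errors are resolved, that assessors join team meetings, or that control-site errors are treated differently. Codebook access for all outcome assessors suggests that both arms were meant to be covered. The reference to a codebook points to questions of coding and definition, which cannot settle what time an accident happened. Nothing describes clock times being queried with the treating teams. These objections stand, and they limit the first part to a risk that depends on attendance.

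It can also be said that REDCap already restricts values, checks ranges and keeps an audit trail in both arms, and that presentation within 24 hours is an entry criterion, which exposes some gross errors in the accident-to-admission interval. This too stands. It lowers the risk but does not show that queries were handled alike.

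A condensed article may leave query procedures and attendance lists to the full protocol. That is fair, and a missing list is not the complaint. The complaint is that the article names a forum which it elsewhere assigns to one arm.

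None of these objections reaches the blinding claim. That rests on where the assessors work and what happens in those hospitals, and both are stated. It is also a separate matter and should not be used to strengthen the point about the meetings.

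It is tempting to put a size on the bias by assuming a rate of time errors corrected in one arm only. The protocol gives no error rate, and correction in one arm only is exactly what has not been shown.

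**Conclusion.** The point holds in two parts of different strength.

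First, data-error resolution is routed through meetings otherwise described only as support for intervention-arm teams. This puts either equal data handling or assessor blinding at risk. It assumes that the identically named meetings are one forum. Which of the two is at risk depends on attendance, which is not stated.

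Second, the claimed blinding of outcome assessors is not delivered by allocation codes. This follows from the stated setting and needs no assumption about attendance. It concerns mainly the interview-based time data and the TOMS, and much less the clinician-documented neurological score or mortality.

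No size can be given for either part. The protocol's one-hour threshold for a meaningful difference is the scale against which any effect would be read, but nothing in the document says how close to it a handling effect could come.

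**What to change.** In Data Management, state that data queries are resolved separately from the trauma-team meetings, by outcome assessors and the central study administrator only, on one schedule and under one set of rules for all six hospitals. If this is how it was done, one clarifying sentence is enough.

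Last follow-up was on August 27, 2023, with analysis planned for Spring 2024, so procedures during collection can no longer be changed. If data were cleaned in the team meetings, use the existing REDCap audit trail to report how many time values were changed, by arm and site, and add a sensitivity analysis of the primary outcomes on the originally entered times. The trail shows only changes made after entry. Data were first recorded on paper, and the paper forms are due for destruction six months after completion, so any comparison with them has to come before that.

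In Concealment Mechanism, Who Will Be Blinded and the section on outcome collection, state that on-site assessors were not effectively blinded. Name this in the limitations for the time intervals and the TOMS.

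The cost is a few sentences of wording, one table from the audit trail and one further analysis. No new data collection is needed.

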### Plans for Collection, Laboratory Evaluation, and Storage of Biological Specimens for Genetic or Molecular Analysis

There are no plans to collect any biological laboratory specimens for storage or for genetic or molecular analysis in this trial.

### Statistical Methods

#### Statistical Methods for Primary and Secondary Outcomes

##### Primary (Process) Outcomes

The primary (process) outcomes of (1) the time interval from the accident to hospital admission and (2) the time interval from the referral decision to hospital discharge will be compared between the intervention and control groups using a 2-sample *t* test if the data are normally distributed or a 2-sample Wilcoxon rank sum test if the data are not normally distributed. The normality of distribution will be assessed using the Shapiro-Wilks test, whereas the equality of variance will be determined using the Levene test. A difference in means of 60 minutes (1 hour) will be considered clinically meaningful in accordance with the golden hour principle [33].

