**Methods:**

This is a 2-arm, parallel, multi-period, cluster randomized, controlled, clinical trial in Uganda, where rural trauma team development training is not routinely conducted. We will recruit regional referral hospitals and include patients with motorcycle accident–related injuries, interns, medical trainees, and road traffic law enforcement professionals. The intervention group (RTTDC) and control group (standard care) will include 3 hospitals each. The primary outcomes will be the interval from the accident to hospital admission and the interval from the referral decision to hospital discharge. The secondary outcomes will be all-cause mortality and morbidity associated with neurological and orthopedic injuries at 90 days after injury. All outcomes will be measured as final values. We will compare baseline characteristics and outcomes at both individual and cluster levels between the intervention and control groups. We will use mixed effects regression models to report any absolute or relative differences along with 95% CIs. We will perform subgroup analyses to evaluate and control confounding due to injury mechanisms and injury severity. We will establish a motorcycle trauma outcome (MOTOR) registry in consultation with community traffic police.

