These variables align well with the proposed global surgery framework to improve national surgical, obstetric, and anesthesia care provider plans [34]. In addition, the variables expand on outcomes for trauma-informed interventions [35]. All outcomes will be measured as final values but will be discussed in relation to the baseline established in our prior feasibility studies [7,30]. The comparisons of outcomes will be made at both individual and cluster levels, using mixed effects regression models.

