##### Secondary (Patient) Outcomes

For assessing the morbidity of musculoskeletal injuries, the validated 10-item TEFS will be used at baseline and the 10-item TOMS will be used at 90 days [30]. The mean difference in the TEFS and TOMS will be compared between the intervention and control groups using the 2-sample *t* test. Further, the TOMS will be dichotomized into favorable (TOMS ≥ TEFS) and unfavorable (TOMS < TEFS) outcomes in accordance with previous studies [30]. The difference in these proportions between the intervention and control groups will be compared using the adjusted chi-square test if the expected count is >5 or the Fisher exact test at 95% CI otherwise.

Further, subgroup analyses will be performed to determine and control for factors that could be associated with an unfavorable TOMS, using individual-level between-within mixed effects regression models, which inherently overcome the effect of smaller clusters and permit adjustment for covariates in a single stage, assuming equal allocation. The fixed effect variables will be the treatment arms (intervention vs control) as the unit of analysis, with the odds ratios (ORs) and their corresponding 95% CIs as direct estimates of the effect size. The covariates will include age, sex, education level, occupation, employment status, marital status, commute distance, road user category, injury severity score based on the KTS, presence or absence of fracture, nature of fracture if present, number of serious injuries, and treatment (surgical vs conservative).

For assessing the morbidity of neurological injuries, the validated GOS will be used at 90 days after injury. The mean difference in the GOS score will be compared between the intervention and control groups using the 2-sample *t* test. Further, the GOS score will be dichotomized into favorable (GOS score of 4 or 5) and unfavorable (GOS score of 3, 2, or 1) outcomes in accordance with previous studies [7]. The difference in proportions between the intervention and control groups will be compared using the adjusted chi-square test if the expected count is >5 or the Fisher exact test at 95% CI otherwise.

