### Study Limitations

Despite the strengths of this trial, we anticipate some limitations. First, while the authors are ambitious to assume that the study centers are homogeneous, the heterogeneity among the 6 participating regional referral hospitals could cause bias and affect study estimates. Further, the relatively smaller number of clusters could affect the power of the study. However, randomization of 6 out of the 17 trauma centers is within the ethical constraints as this sample already represents 35.3% of Uganda’s regional referral hospitals. To overcome the statistical power bias limitation, the sample size is inflated for individual randomization to cater to the design effects in accordance with the report by Hooper et al [45]. Moreover, we plan to use mixed effects regression models, which permit adjustments for covariates at both the cluster and individual levels in a single-stage approach, and plan to use the *t* test, which is robust in terms of normality deviations. According to Borhan et al [52], mixed effects models are deemed suitable for smaller clusters in situations where the primary outcomes are continuous, which is the case in this trial. Further, we hope that the ancillary studies with mixed methods will add value to the overall interpretation of the trial results by providing data from individuals outside the health sector, such as traffic law enforcement professionals.

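### The primary intervals are assigned unadjusted two-sample tests in one section and mixed models elsewhere, and no covariate is named for them; the gain from adjusting is modest

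*Protocol article*

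**What the plan says.** **Named test.** Under Primary (Process) Outcomes, accident-to-admission time and referral-decision-to-discharge time "will be compared between the intervention and control groups using a 2-sample *t* test if the data are normally distributed", with a Wilcoxon rank sum test otherwise. A 60-minute difference in means is called clinically meaningful. No covariate or hospital effect appears there.

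**Promised model.** The abstract states: "We will use mixed effects regression models to report any absolute or relative differences along with 95% CIs". The Outcomes section states: "The comparisons of outcomes will be made at both individual and cluster levels, using mixed effects regression models". Study Limitations relies on "mixed effects regression models, which permit adjustments for covariates at both the cluster and individual levels in a single-stage approach" and adds that "mixed effects models are deemed suitable for smaller clusters in situations where the primary outcomes are continuous, which is the case in this trial".

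**Covariates.** Commute distance appears only in the model for the Trauma Outcome Measure Score (TOMS): "The covariates will include age, sex, education level, occupation, employment status, marital status, commute distance, road user category". Time of injury and road user category are in the data collection list. That section also plans to adjust for the baseline Trauma Expectation Factor Score (TEFS), Glasgow Coma Scale (GCS) and Kampala Trauma Score (KTS), on the ground that "the inclusion of baseline values of outcomes as covariates is arguably one of the strongest factors to reduce ICC estimates".

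**Design.** Under Sequence Generation, "we will not add any stratification factors in the simulation model".

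**The concern.** The section that fixes the primary analysis and the sections that describe the analysis in general name different methods. The two methods give different standard errors and can give different estimates, so an analyst could follow either one and claim to have followed the plan.

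The covariate question sits inside that conflict. Accident-to-admission time depends partly on circumstances already set when the accident happens. With three hospitals against three and no stratification, a chance difference between the arms in those circumstances goes into the estimate that is judged against 60 minutes. The secondary TOMS and mortality models have long covariate lists and the primary intervals have none. The three scores named for general adjustment do not fill the gap. GCS is scored at admission, and baseline clinical data are collected then, so GCS and KTS come when the first interval has ended. TEFS is taken in the first week or before discharge.

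At stake are an unambiguous primary result, some precision, and how readily a difference can be credited to the training rather than to which hospitals fell in which arm.

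**Working it through.** **1. Inputs from Sample Size.** Difference 1.02 h, SD 1.64 h, within-period ICC 0.02 (0.01 to 0.05), cluster autocorrelation 0.8, 12 periods of 10 patients (120 per hospital), cluster-size CV 0.5, 3 hospitals per arm, alpha 0.05 (taken as two-sided), t distribution with 6 − 2 = 4 df. The correlation of covariates with the interval is not given. I assume 0.5, so 0.5² = 25% of variance explained, and also show 0.3 and 0.7.

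**2. Formulas.**
- Between-hospital part B = SD² × ICC × S, where S is the mean of 0.8^|i−j| over 12 periods = 0.491.
- Within-hospital part W = SD² × (1 − ICC)/120.
- Variance of a hospital mean = (B + W)/RE, where RE = 1 − CV² × λ(1 − λ) and λ = B/(B + W).
- SE of the arm difference = √(2 × variance/3).
- Power from the noncentral t.

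**3. The plan's own power, without covariates.** At ICC 0.05:
- B = 2.6896 × 0.05 × 0.491 = 0.0661 and W = 2.6896 × 0.95/120 = 0.0213, sum 0.0874.
- λ = 0.756, RE = 0.954, variance 0.0916, SE 0.247 h, power 86.4%.

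At ICC 0.02 the SE is 0.185 h and power 97.9%. The stated 80% is therefore met without adjustment, even at the upper ICC.

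**4. With covariates.** Half-width is that of the 95% CI.

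| ICC | Case | SE (h) | df | Power | Half-width (h) |
|---|---|---|---|---|---|
| 0.05 | none | 0.247 | 4 | 86.4% | 0.686 |
| 0.05 | 25% explained at both levels | 0.214 | 4 | 93.8% | 0.594 |
| 0.05 | same, one hospital-level df spent | 0.214 | 3 | 87.3% | 0.681 |
| 0.05 | 25% explained within hospitals only | 0.239 | 4 | 88.5% | 0.662 |
| 0.02 | none | 0.185 | 4 | 97.9% | 0.515 |
| 0.02 | 25% explained at both levels | 0.161 | 4 | 99.5% | 0.446 |
| 0.02 | same, one hospital-level df spent | 0.161 | 3 | 97.9% | 0.511 |

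The critical value rises from 2.78 (4 df) to 3.18 (3 df), which almost cancels the smaller SE. At ICC 0.05 with variance explained at both levels:
- correlation 0.3 gives 89% on 4 df and 81% on 3 df, the latter below the unadjusted 86%;
- correlation 0.7 gives 99% on 4 df and 96% on 3 df.

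**5. Chance imbalance between arms.** SD = 1.64 × √(ICC × 0.491) × √(2/3).
- ICC 0.02: 0.133 h, about 8 minutes.
- ICC 0.05: 0.210 h, about 13 minutes.

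This counts every source of hospital-level variation. If covariates explain 25% of it, their share has half that SD: about 4 and 6 minutes.

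**6. Why the choice of method matters apart from covariates.** A two-sample test without a hospital term understates the SE. At ICC 0.02 with equal hospital sizes, the variance ratio is [0.02 × 0.491 + 0.98/120] × 120 = 2.16. The nominal 5% error becomes 2 × [1 − Φ(1.96/√2.16)], about 18%.

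**The case against.** **The unseen analysis plan may settle this.** A covariate list is commonly left to a statistical analysis plan, and the article refers to an appendix for analysis metrics. Had the article been silent, there would be no point to raise. It is not silent: it names one method in the section on the primary outcomes and another in three other places. That conflict stands on the text.

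**A reader might infer that the primary analysis is simply unadjusted.** The documents do not support that. Study Limitations ties mixed models, with possible covariate adjustment, to the continuous primary outcomes.

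**A reader might infer that distance biases the result.** Allocation is random, so differences in catchment are chance variation, and a correctly clustered SE already allows for them.

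**A reader might infer a large gain in power.** The rise from 86% to 94% needs the extreme ICC, an assumed correlation of 0.5 at both levels, and no loss of degrees of freedom. Without these it shrinks to 1 or 2 points. This objection stands.

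**A reader might treat commute distance as the obvious covariate.** It is undefined and appears only in the TOMS model. Under Intervention Description, trained teams coordinate evacuation, referral and arrival at recipient centers, so the hospital reached, and hence the distance to it, may be affected by the intervention. Adjusting for that distance could remove part of the effect or introduce bias. This objection also stands.

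**Nothing shows that these covariates predict referral-to-discharge time.** Agreed; no benefit is claimed there.

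**Conclusion.** The point holds in a limited form. The article states the primary analysis in two incompatible ways, and under neither does it name a covariate for the primary intervals, although allocation is unstratified and two predictors fixed at the accident are collected.

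The statistical gain from adjustment is modest. At the planning ICC of 0.02 it is under 2 points of power. At the upper ICC of 0.05 and correlation 0.5 it is between about 1 and 7 points, depending on whether a hospital-level degree of freedom is spent and whether the covariates explain differences between hospitals. These figures rest on an assumed correlation and on 120 patients per hospital. The planned power does not depend on adjustment. The firmer reasons to act are that a single primary analysis is fixed in advance and that covariates are not chosen after the data are seen.

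**What to change.** Rewrite Primary (Process) Outcomes so that it agrees with the abstract, Outcomes and Study Limitations:

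- Make the primary estimate for each interval the arm difference in hours, with 95% CI, from a mixed model with a hospital effect and a stated small-sample degrees-of-freedom method.
- For accident-to-admission time, prespecify a short list of patient-level covariates fixed at the accident: time of injury (day or night) and road user category. Do not use admission GCS or KTS.
- Define commute distance. Use it in the primary model only if it is recorded in a form that the intervention cannot change, such as home or accident-scene location rather than distance to the hospital reached. Otherwise keep it for a sensitivity analysis.
- Report the clustered estimate without covariates as a sensitivity analysis.
- Claim no specific covariate benefit for referral-to-discharge time.

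**Cost.** Wording and a little code before the analysis scheduled for Spring 2024, with no new patients or procedures. Missing covariate records need a stated rule. Entering hospital-level covariate means may cost a degree of freedom, which with six hospitals can cancel the gain. Deriving distances from recorded locations would be extra work.
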